### 2.1. Trial Design

The “FINE” project is a 3-month (12 weeks) intervention program, single-blind, two-armed cluster randomized controlled trial (cluster RCT), conducted among pre-frail elderly with a pre- and post-intervention and 3-month follow-up assessments to assess the effectiveness of the program. The trial mainly comprises nutritional education and exercise intervention among older people aged 60 years and above in the PPR flats in Kuala Lumpur. The trial is registered prospectively at ClinicalTrial.gov with registration number NCT04327544 on 30 March 2020.

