#### 2.4.1. Primary Outcome

##### Frailty Score/Status

The frailty status will be assessed using the well-established Malay language standardized phenotype of the frailty questionnaire; as proposed by Fried et al. [5]. The questionnaire evaluates five components of the frailty syndrome (weight loss, exhaustion, weakness, slowness, and low activity) and allocates one point for each criterion met; respondents meeting zero criteria are defined as non-frail, whereas those meeting one or two criteria are defined as pre-frail, and those meeting three, four, or five criteria are defined as frail.

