### 2.5. Statistical Analysis

The description of the respondents’ characteristics will be reported by group (control and intervention). Depending on the distribution of the variable of interest, the descriptive statistics of continuous data will be presented by using the mean and standard deviation and the median and the inter-quartile range. Categorical data will be presented as frequencies and percentages. For primary analysis, since there are small number of cluster, as recommended by Hayes and Moulton (2017), analysis will be conducted at cluster level instead of individual level [58]. Thus, the primary and secondary outcomes will be compared within and between groups using 2-way repeated ANOVA by general linear model. Any covariate data at baseline value will be adjusted and further test will be conducted using a repeated measure analysis of covariance (ANCOVA). If the data is not distributed normally, Kruskall–Wallis test will be used to analyze the data. Statistical significance is set at *p* < 0.05. Data will be entered and analyzed using SPSS 25.0 software.

Intention-to-treat (ITT) will be applied in the data management and analysis. All data will be processed according to their arm even if the participant did not manage to come to all the intervention sessions. It is assumed that majority of the participant in the intervention arm will receive adequate number of the intervention sessions. Action will be taken in order to prevent lower attendance from the participants such as conducting extra exercise classes for participants who could not come to a certain session. For every nutrition session, class will start with the revision on the topic that had been discussed in previous session. This can help participants who could not come to the previous nutrition session to learn the topic they missed.

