## Figures and Tables

**Figure 1 nutrients-12-02758-f001:**
[figure not shown]
The overview of the frailty intervention study flow. Adapted from the CONSORT 2010 flow diagram (extension to cluster randomized trails) [41].

**Table 1 nutrients-12-02758-t001:** The summary of the inclusion and exclusion criteria for the Frailty Intervention through Nutrition Education and Exercise (FINE) program.

Inclusion Criteria	Exclusion Criteria
Men or women aged 60 years and above	Self-reported chronic diseases and mental illnesses (heart-related disease, chronic obstructive pulmonary disease (COPD), stroke, cancer, asthma, renal dysfunction, terminally ill, major depression, bipolar, disorder, obsessive compulsive disorder and post-traumatic disorder)
Meet one or two frailty phenotype score (pre-frail)	Physical Activity Readiness-Questionnaire (PAR-Q & YOU)(Yes ≥ 1) [43]
Able to ambulate without personal assistance	Bedridden
Residing in the PPR flats in Kuala Lumpur	Cognitive impairment (Elderly Cognitive Assessment Questionnaire, ECAQ < 6) [44]
Willing to participate in the intervention program with informed consent	Sensory impairment (visual & hearing) that will interfere with communication
	Unable to read and write
	Already involved or still participating in any health interventional study
	Any sustained fracture (hip, vertebrae) in past six months
	Any surgery (hip, abdominal area) in past six months

**Table 2 nutrients-12-02758-t002:** Summary of the frailty FINE program.

Intervention Group					Control Group
12 weeks intervention program	**Week**	**Day 1**	**Day 2**	**Day 3**	* No intervention
	1	Talk on frailty	Talk on exercise	Talk on healthy eating	
	2	Multicomponent exercise *			
	3	Multicomponent exercise *		Nutrition education class	
	4	Multicomponent exercise *			
	5	Multicomponent exercise *		Nutrition education class	
	6	Multicomponent exercise *			
	7	Multicomponent exercise *		Nutrition education class	
	8	Multicomponent exercise *			
	9	Multicomponent exercise *		Nutrition education class	
	10	Multicomponent exercise *			
	11	Multicomponent exercise *		Nutrition education class	
	12	INTERVENTION END			

* exercise intervention.

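### The non-normality switch to Kruskal–Wallis drops the planned group-by-time comparison and baseline adjustment, and lets the data choose the primary test

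*Protocol article*

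**What the plan says.** Four statements in the protocol article bear on this point.

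- **Unit.** Section 2.5 gives the small number of clusters as its reason, and says that for the primary analysis "analysis will be conducted at cluster level instead of individual level".
- **Main model.** The same paragraph says that "the primary and secondary outcomes will be compared within and between groups using 2-way repeated ANOVA by general linear model". On baseline it continues: "Any covariate data at baseline value will be adjusted and further test will be conducted using a repeated measure analysis of covariance (ANCOVA").
- **Fallback.** It then says: "If the data is not distributed normally, Kruskall–Wallis test will be used to analyze the data".
- **Outcome and visits.** The primary outcome is the frailty phenotype. It covers five components and "allocates one point for each criterion met" (section 2.4.1), so the score is an integer from 0 to 5. Table 1 admits only people who score 1 or 2 at entry. Section 2.1 describes a trial "with a pre- and post-intervention and 3-month follow-up assessments", which makes three assessments.

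Section 2.5 does not say whether normality is judged on individual scores, flat summaries or residuals. Nor does it say whether Kruskal–Wallis is run on people or flats, or at which visit.

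**The concern.** With two arms, Kruskal–Wallis is the rank-sum test. It compares two sets of independent values and has no place for time, for a group-by-time term or for a covariate. A rule that swaps the planned model for this test changes the question as well as the distributional assumption. The comparison of change between arms over three assessments becomes a comparison of two unadjusted sets of ranks at an unspecified time.

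The rule also makes the primary test conditional on the data. An integer score of 0–5, restricted to two values at entry, invites a failed normality check if individual scores are examined.

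What follows depends on the unit tested. On individuals, the test ignores the flats. On flats, eight values leave a rank test with very few attainable p-values.

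**Working it through.** **Inputs.** From section 2.2.4: ICC 0.02, planning cluster size 4, 15 per arm before clustering, 4 clusters per arm, 60 respondents in total, α = 0.05. Two-sided testing is assumed because sidedness is not stated. From 2.4.1 and Table 1: score 0–5, and 1 or 2 at baseline.

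**1. The plan's own figure.** Design effect = 1 + (m − 1) × ICC = 1 + 3 × 0.02 = 1.06. Then 15 × 1.06 = 15.9, rounded up to 16 per arm, and 16 / 4 = 4 clusters. The stated figures reproduce. Recruited cluster size is 60 / 8 = 7.5, which the article gives as about 8.

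**2. How often the switch is triggered.** The article names no normality test and gives no score distribution, so both are assumptions here: a Shapiro–Wilk test at 0.05, ICC 0.02 on a latent scale, and 8 flats. Baseline scores were split 50:50 or 70:30 between 1 and 2. Four post-intervention distributions over 0–5 were tried. Share of simulated trials in which normality is rejected:

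| What is checked | Baseline | Post-intervention |
|---|---|---|
| 30 individual scores | 100% | 75–100% |
| 60 individual scores | 100% | about 100% |
| 8 flat means, 8 people each | 18–23% | 7–9% |
| 8 flat means, 4 people each | 34–45% | 10–16% |

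The switch is nearly certain on individual scores and uncommon on post-intervention flat means.

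**3. Kruskal–Wallis on individuals.** Approximate type I error = 2 × [1 − Φ(1.96 / √DE)], with DE = 1 + (m − 1) × ICC.

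- m = 7.5, ICC 0.02: DE = 1 + 6.5 × 0.02 = 1.13, giving 6.5%.
- m = 8, ICC 0.02: DE = 1.14, giving 6.6%.
- Two simulations of a clustered ordinal score at ICC 0.02 gave 5.9% and 6.0%.
- At assumed ICCs not in the article, approximation and simulation together give about 8–10% (ICC 0.05) and 12–13% (ICC 0.10).

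**4. Kruskal–Wallis on eight flat summaries, no ties.** There are C(8,4) = 70 equally likely splits under the null. H = [12 / (8 × 9)] × (R₁² + R₂²) / 4 − 3 × 9, where R₁ and R₂ are the rank sums.

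| Result | Rank sums | H | Exact p | Chi-square p |
|---|---|---|---|---|
| Complete separation | 10, 26 | 194/6 − 27 = 5.33 | 2/70 = 0.029 | 0.021 |
| One adjacent pair swapped | 11, 25 | 186.5/6 − 27 = 4.08 | 4/70 = 0.057 | 0.043 |

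With exact p-values only complete separation is significant. With the chi-square approximation the second ranking is significant too, at a true size of 4/70 = 5.7% without ties. In the simulations, where flat means of integer scores can tie, the approximate test on flat means rejected in about 5% of null trials at each ICC from 0.02 to 0.10.

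**5. Structure lost.** This needs no simulation. The main model has group, time, their interaction and baseline covariates. The fallback has group only.

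**The case against.** The strongest reply is that the paragraph has already fixed the unit. The fallback follows the cluster-level statement, so the data in question are most naturally the flat values. On that reading the switch is seldom triggered after baseline, clustering is respected, and type I error stays near 5%. This stands. A reader might infer that the fallback will almost certainly become the real primary analysis, or that it discards clustering. The article supports neither as a general statement. Both require that individual scores are checked and tested. The individual reading is still open: the fallback sentence names no unit, and the same section chooses descriptive statistics by each variable's distribution.

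A reader might also infer a definite loss of power. At 1.02 SD and ICC 0.02, simulation gives about 48–49% for the exact rank test against 65–66% for a t-test with 4 people per flat, and 72–73% against 87% with 7.5. That gap belongs to exact p-values alone. With the chi-square approximation the rank test matches the t-test (65% and 87%). The 1.02 SD is moreover back-calculated from the sample size of 15 per arm, which rests on the SPPB, a secondary outcome, and not on the frailty score. No power loss should be claimed.

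A rank test could be run on flat mean changes or on baseline-adjusted residuals, and section 2.4 does list change in frailty score as an outcome. So the loss of baseline lies in the rule as worded and not in rank tests as such. That is a reason to rewrite the sentence.

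Finally, a normality criterion or a visit is the kind of detail that an analysis plan may hold, and its absence alone would not be a finding. The objection here is to a rule that the article does state, which conflicts with the model in its own paragraph.

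**Conclusion.** The point holds in a limited form. On any reading of the sentence as written, non-normality replaces a group-by-time, baseline-adjusted analysis with an unadjusted one-way rank test, and the data decide which test is primary.

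The numerical consequences are conditional:

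- **Individual scores checked and tested:** the switch is nearly certain, the cluster-level rule is contradicted, and type I error is about 6–6.5% at the protocol's ICC. This is a modest inflation, larger only if a higher ICC is assumed.
- **Flat summaries tested:** clustering is kept, but the ranking one step short of complete separation has p = 0.057 or 0.043, depending on a choice that the article does not state.

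The trigger rates rest on assumed score distributions and an assumed Shapiro–Wilk check. The p-values for eight flats assume no ties and treat flats as exchangeable between arms. The structural conflict rests on none of these. It should be corrected, though the size at the planned ICC does not make it a fatal flaw.

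**What to change.** Delete the normality-triggered switch in section 2.5. In its place, fix in advance one primary comparison: flat mean frailty score at one named visit, adjusted for baseline, analysed at cluster level whatever the distribution of individual scores. Each flat value averages several people, so non-normal individual scores are no reason to change test. A rank or permutation test on the flat summaries can be kept as a sensitivity analysis only, with a statement of whether its p-value is exact or approximate.

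This costs a sentence or two of text and no data. The price is that a single-visit primary comparison leaves the other post-baseline visit to a secondary analysis.

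The change does not address a separate problem. Section 2.2.5 randomises at zone level, with two zones, so flats are not allocated independently. Neither a t-test on eight flats nor a permutation over 70 splits should be described as matching the randomisation.

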## 3. Discussion

The FINE intervention program presents a unique approach, delivering a multi-domain intervention for pre-frail elderly men and women who live in the urban community. Often, research had been made among poor rural elderly, showing their high risk of getting malnutrition and becoming frail, but less is known among poor elderly population that live in urban areas such as the elderly community in PPR, Kuala Lumpur. Considering the high prevalence of the pre-frail elderly in urban areas [15], this target group should not be neglected. Aligned with the main objectives to improve the frailty status of the elderly, the program will have a highly positive impact in many ways, i.e., physically, mentally, and in social life.

The major strength of the proposed study design is the implementation of a multi-domain intervention that was considered to be more effective that a single intervention, especially through nutrition and exercise [33,34]. In addition, the designated nutritional education intervention was made based on the study that had demonstrated positive outcomes among frail elderly [18,26,59]. A few elderly-related local nutrition-education programs were also reviewed during the design process [1,60], considering the cultural values of local elderly population.

The strength of the nutrition education in this study mainly highlights the strategy to tackle the unintentional weight loss problem, which is also one of the main problems among frail elderly people [61]. Targeting one of the risk factors of frailty is also one of the key strategies for frailty prevention, as highlighted in the report of Asia Pacific CPGs for the management of frailty. The multicomponent exercises were applied in this study because of the strong evidence that performing different types of exercise assists in frailty prevention and improves the outcomes [35,36], and it is strongly recommended by Asia Pacific CPGs. The multi-component exercises were adapted from the exercise programs that were feasibly delivered to frail older people [29,32] with slight modifications to ensure better adherence to the exercise program by the local elderly.

An additional advantage of this community-based intervention is that it will be conducted in a natural setting, allowing respondents to integrate changes into their daily lives in a real-life context. This implies that the intervention delivered can be potentially transferable to other community settings. Moreover, it is also readily transferable to routine clinical practice in a health service setting, and the interdisciplinary approach is relevant to several professional groups in health care such as nutritionists, dietitians, and physiotherapists.

## 4. Conclusions

In overall, this FINE intervention program has been designed to be interactive, enjoyable, and manageable to encourage adherence among the respondents. Based on the evidence, we are convinced that this intervention program will be able to prevent frailty and the adverse effects associated with pre-frail elderly people. If the intervention produces significant positive effects, the findings will potentially provide valuable evidence and serve as a model of locally acceptable strategies to prevent frailty and reduce adverse health outcomes among older Malaysians.

## Figures and Tables

**Figure 1 nutrients-12-02758-f001:**
[figure not shown]
The overview of the frailty intervention study flow. Adapted from the CONSORT 2010 flow diagram (extension to cluster randomized trails) [41].

**Table 1 nutrients-12-02758-t001:** The summary of the inclusion and exclusion criteria for the Frailty Intervention through Nutrition Education and Exercise (FINE) program.

Inclusion Criteria	Exclusion Criteria
Men or women aged 60 years and above	Self-reported chronic diseases and mental illnesses (heart-related disease, chronic obstructive pulmonary disease (COPD), stroke, cancer, asthma, renal dysfunction, terminally ill, major depression, bipolar, disorder, obsessive compulsive disorder and post-traumatic disorder)
Meet one or two frailty phenotype score (pre-frail)	Physical Activity Readiness-Questionnaire (PAR-Q & YOU)(Yes ≥ 1) [43]
Able to ambulate without personal assistance	Bedridden
Residing in the PPR flats in Kuala Lumpur	Cognitive impairment (Elderly Cognitive Assessment Questionnaire, ECAQ < 6) [44]
Willing to participate in the intervention program with informed consent	Sensory impairment (visual & hearing) that will interfere with communication
	Unable to read and write
	Already involved or still participating in any health interventional study
	Any sustained fracture (hip, vertebrae) in past six months
	Any surgery (hip, abdominal area) in past six months

**Table 2 nutrients-12-02758-t002:** Summary of the frailty FINE program.

Intervention Group					Control Group
12 weeks intervention program	**Week**	**Day 1**	**Day 2**	**Day 3**	* No intervention
	1	Talk on frailty	Talk on exercise	Talk on healthy eating	
	2	Multicomponent exercise *			
	3	Multicomponent exercise *		Nutrition education class	
	4	Multicomponent exercise *			
	5	Multicomponent exercise *		Nutrition education class	
	6	Multicomponent exercise *			
	7	Multicomponent exercise *		Nutrition education class	
	8	Multicomponent exercise *			
	9	Multicomponent exercise *		Nutrition education class	
	10	Multicomponent exercise *			
	11	Multicomponent exercise *		Nutrition education class	
	12	INTERVENTION END			

* exercise intervention.
